## Abstract

**Background:**

Gynecological cancers pose significant physical, psychological, and social challenges for those affected. Although psychosocial interventions are components of holistic cancer care, access can be limited by specialized practitioner expertise, wait times, gender-biased care, and accessibility constraints. These barriers highlight a recognized need for alternative, timely, and nonclinical approaches that can complement existing services and relieve system pressures.

**Objective:**

The primary study aim is to evaluate the feasibility and acceptability of an online shared reading program as a novel, adjunctive psychosocial intervention for people affected by gynecological cancers. The secondary aim is to explore the intervention’s preliminary individual-level outcomes on psychological distress, well-being, and quality of life.

**Methods:**

This mixed methods feasibility study uses a multiple-baseline single-case design informed by a realist evaluation theoretical framework. Up to 10 participants aged 18 years or older with a primary diagnosis of gynecological cancer will be recruited internationally. The intervention consists of 6 weekly 1-hour literature reading group sessions delivered via Microsoft Teams. Three baseline assessments at −2 weeks, −1 week, and week 0 will establish outcome stability prior to the intervention, followed by midintervention (week 3) and postintervention (week 6) assessments. Outcome measures include the Short Warwick-Edinburgh Mental Wellbeing Scale, the Kessler Psychological Distress Scale, the WHOQOL-BREF social domain subscale, and 2 global quality of life items from the EORTC QLQ-C30. Individual-level change within these measures will be examined using the reliable change index at a threshold of 1.96 or higher, presented as modified Brinley plots. Feasibility will be assessed and summarized descriptively using recruitment and retention rates, session attendance and completion rates, and reasons for dropout. Acceptability will be examined through semistructured interviews of up to 30 minutes conducted by an independent researcher after the intervention. Interview data will be analyzed using reflexive thematic analysis to explore participants’ intervention experience and perceived mechanisms of change.

**Results:**

This feasibility study was funded in October 2022 as part of a PhD scholarship. Recruitment began in November 2025 and continued until March 2026. At the time of manuscript submission in January 2026, a total of 6 people had registered their interest, of whom 2 met the eligibility criteria. The data analysis plan was formulated but not implemented, with the intervention set to begin in May 2026. Findings are expected to be submitted for publication in November 2026.

**Conclusions:**

Potential implications include that the digital, low-intensity, group-based online shared reading format may offer a novel psychosocial support alternative to survivors of gynecological cancer who may be otherwise excluded due to residing in geographically remote areas, financial constraints, or reluctance to engage with formal psychological therapy. If feasible and acceptable, the intervention may contribute to equitable cancer care provision and inform the design of future implementation studies in digital oncology services.

## Introduction

### Background

Gynecological cancers—including malignancies of the cervix, ovaries, uterus, vagina, and vulva—represent a significant health challenge for women and gender-diverse people assigned or presumed female worldwide [1-3]. Prevalence and age incidence vary across settings—cervical cancer disproportionately affects those in low- and middle-income countries largely due to higher human papillomavirus prevalence and limited screening [4,5], whereas endometrial cancer is increasing in high-income regions, linked to obesity and aging populations [6,7]. Even as advances in diagnosis and treatment have improved survival rates, those affected can experience psychological distress, including anxiety, depression, fear of recurrence, anger, shame, low self-esteem, and reduced quality of life (QoL) [3,8], often compounded by disruption to reproductive and sexual health [9,10]. Gynecological cancers also carry gendered stigma, with transgender people experiencing a particular sense of disconnect when they are diagnosed with a cancer that does not align with their gender identity [11,12]. As a result, they often report feeling uncomfortable attending support groups organized according to sex assigned at birth [13,14].

However, despite its recognition as an essential component of cancer care, psychosocial care remains inconsistently embedded worldwide [15,16]. Across both high- and low-income countries, survivorship support is often fragmented, reactive, and primarily biomedical, focusing on disease surveillance rather than long-term emotional and social recovery [17,18]. Existing psychosocial interventions—including counseling, cognitive behavioral therapy, and mindfulness-based approaches—have shown efficacy in reducing anxiety and depression in survivors of cancer [19,20]. However, the evidence base remains heterogeneous, with substantial variation in intervention content, delivery format, and outcome measurement, making it difficult to determine what works best, for whom, and under which circumstances [21]. Structural barriers including workforce shortages, long wait times, and stigma around mental health can further exacerbate inequalities and restrict access [22-24]. Additionally, clinical guidelines [25] offer limited direction on how best to embed psychosocial care across the patient pathway. This creates the need for accessible, scalable, and adjunctive approaches deliverable outside specialist services, particularly for those who fall below the threshold for formal psychological support.

One promising strategy is using creative arts and literature–based digital health interventions (hereafter referred to as “arts and health”) as a form of community psychosocial support [26,27]. Their online format can improve accessibility for people living in remote or underserved areas and lessen the stigma associated with formal psychological therapy [28,29]. Additionally, arts and health interventions remain relatively low cost, resource efficient, and scalable to diverse populations [30,31]. Within this field, shared reading (SR) is an established model of facilitated literary engagement. It involves trained reader leaders who select short stories, novel extracts, or poems to read aloud. During the reading, planned reflective pauses are used to invite participants’ thoughts, feelings, and associations around classic literature [26,32-34]. This deliberate use of meaningful pauses is a defining feature of SR intended to foster deep engagement with the material read and support immediate, in-the-moment reflections [35]. Studies of SR across diverse populations, including prisons, dementia care, substance use recovery, and chronic pain, report improvements in psychological well-being, emotional regulation, and self-awareness [36-38]. These benefits are perhaps reflective of the nonclinical settings in which the intervention takes place—often a library, community center, or virtual room—where emotional expression and a sense of belonging are created via the collective experience of literature reading. Notably, the values that underpin SR also closely align with trauma-informed frameworks, building around safety, choice, collaboration, trust, and empowerment as core principles of care [39,40]. In SR, participants can speak or stay silent, engage with the text directly or through its characters, and decide how much of their own story to bring into the room. These features make SR a conceptually strong strategy for adaptation to people living with and beyond gynecological cancer, for whom issues of control, identity, and safety are often central [41,42].

However, there is still uncertainty around the methodological and evaluative value of arts and health interventions due to poor study design, insufficient focus on feasibility studies, and a lack of consensus on how to measure their value [43,44]. Recommendations include incorporating mixed methods research to capture both the qualitative and quantitative impacts of arts and health interventions [45,46]. Feasibility and pilot studies are also thought of as foundations for later randomized controlled trials, providing critical evidence on design optimization, resource needs, and recruitment strategies [47,48]. Such preparatory work can offer insights often missing from efficacy trials and could inform policy, funding decisions, and the justification for larger-scale implementation.

Consistent with the Medical Research Council’s [49,50] guidance on explaining *why* an intervention works rather than exclusively on *if* it does, this feasibility study is underpinned by a realist evaluation (RE) approach [51]. RE seeks to explore what works, for whom, and in what circumstances through context-mechanism-outcome configurations. Specifically, “context” refers to the conditions under which the online SR may work, such as illness stage, prior interest in literature, or openness to discussing emotions. “Mechanism” relates to the intervention processes that may drive change, including emotional resonance with the literature or others in the group, self-reflection, or narrative reappraisal. Finally, “outcome” refers to the benefits that online SR may produce, including reduced distress; improved well-being or QoL; and feasibility measures such as attendance, engagement, and acceptability. Importantly, RE complements the study’s rationale because it recognizes that the intervention may be meaningful for some participants and less so for others depending on their unique cancer experiences, needs, and readiness to engage.

### Study Objectives

The primary study objective is to assess the feasibility and acceptability of a 6-week online SR intervention for women and gender-diverse people affected by gynecological cancers. The secondary objective is to explore the intervention’s preliminary individual-level effects on psychological well-being, distress, and QoL.

## Methods

### Intervention Development and Content

The intervention draws on the established face-to-face SR model developed by The Reader [35] but takes place within a virtual Microsoft Teams environment. Specifically, the intervention development followed 3 sequential steps: first, the lead author ([name]) completed the mandatory 3-week *Read to Lead* facilitator program created by The Reader [35]. Training included guidance on facilitating open-ended literary discussions, using reflective pauses and questions, and maintaining respect and safety within a group environment. The latter aspect involves reiterating, at the start of each week, that sessions are not recorded and that any data handling will comply with the UK Data Protection Act 2018 and the General Data Protection Regulation.

Second, all selected literature was chosen either from The Reader’s anthology bank or in consultation with The Reader [35] (Multimedia Appendix 1). Texts with explicit references to cancer, illness, or death were excluded to avoid inadvertently influencing the content of the discussions or participants’ emotional responses.

Third, the digital adaptation of the sessions was refined in collaboration with and in response to feedback from a 1-hour patient and public involvement and engagement (PPIE) group; this informed both the content and online delivery format of the intervention. Specifically, in May 2024, a total of 6 community members were recruited via social media and asked to review and provide feedback on study materials and content and the appropriateness of online vs face-to-face delivery. Participants discussed the potential benefits of online sessions, including the lessening of cost and time burdens associated with traveling, as well as the potential widening of participation nationally and internationally. One PPIE participant was recruited to provide ongoing input throughout the research process. Their role includes supporting with participant recruitment, reflecting on qualitative data interpretation, and collaborating on the dissemination of findings. All contributions are reimbursed in line with National Institute for Health and Care Research guidance of £25 per person per hour (£1=US $1.35 as of August 7, 2026).

The finalized intervention model will consist of 6 weekly group sessions, each lasting 1 hour and delivered via Microsoft Teams. Sessions will be scheduled on the same day and time each week, to be confirmed with participants prior to intervention start. This decision will support a sense of continuity and allow participants to plan around existing commitments. Additionally, to preserve spontaneity, texts will be shared with participants via email 15 minutes before each session. Participants will be required to keep their cameras on to maintain a sense of group presence and connection; however, they will be free to contribute to discussions either verbally or via the chat function. Texts will be screen shared during sessions to ensure that all participants can easily follow along, thereby preserving the live, interactive presence of the literature. Session format and structure is shown in Table 1. Additionally, a TIDieR (Template for Intervention Description and Replication) checklist is provided as Checklist 1.

**Table 1. T1:** Online shared reading session structure repeated each session^a^.

Session components	Description
Review rules of engagement (approximately 10 min)	Study introduction (ie, what shared reading is; sessions take place every week for 6 wk; duration of between 60 and 90 min; scheduled at the same time and day of the week) Confidentiality agreement (ie, data handling; GDPR^b^; sessions are not recorded) Microsoft Teams tutorial covering essential platform features (audio and video settings and raising their hand or unmuting to speak; option to use the chat function) Agreement to have cameras on
Reading aloud (approximately 5-10 min)	Reader leader reads the opening lines, a section, or the full text (ie, a poem) aloud
Pause and reflect (approximately 15 min)	Silence held to allow for responses from the group by asking whether there are any thoughts or reflections on what was read
Participants invited to read (approximately 5-10 min)	Participants are asked whether they would volunteer to reread lines or passages aloud in their own voice and style.
Group discussion (approximately 15 min)	Facilitated by the reader leader, participants share thoughts, reflections, and responses (ie, which line or image felt easiest to picture and why, what feeling the poem left behind, which part felt most familiar or surprising, which line they would want to discuss further, and why they thought the author used those visual images to make their mark)

a Consideration of backup literature and session timings: if participants struggle to engage, a backup text is introduced, and the process is repeated from step 2.

b

GDPR: General Data Protection Regulation.

### Participants

Up to 10 women and gender-diverse people aged 18 years or older diagnosed with a primary form of gynecological cancer will be invited to participate in the intervention. To be eligible, participants must not be receiving other psychological interventions at the time of recruitment. This exclusion reflects the potential for concurrent specialized therapies to confound interpretation of online SR’s preliminary individual-level effects on psychological distress, well-being, and QoL. The full eligibility criteria are shown in Textbox 1.

Textbox 1.Feasibility study inclusion and exclusion criteria.
**Inclusion criteria**
Women and gender-diverse people aged 18 y or olderGynecological cancer (ie, cervical, ovarian, uterine, vaginal, vulvar, or fallopian tube) as primary diagnosisEither in active treatment or in remission
**Exclusion criteria**
Current or previous participation in shared reading specificallyWomen and gender-diverse people with cancer of unknown primary or gynecological cancer as secondary (ie, affected by multiple cancers, but primary cancer is unknown)Current receipt of other psychological interventions (ie, counseling or cognitive behavioral therapy)Inability to comprehend the study and/or provide informed consent (ie, insufficient command of the English language in the absence of someone who can adequately interpret)

As this is not a full-scale trial, nor is the primary aim to evaluate the effectiveness of online SR, a formal sample size calculation was not required [52,53]. Instead, the target sample was determined based on 2 factors. First, single-case experimental design (SCED) methodology requires a minimum of 3 participants to demonstrate an experimental effect [54]. Second, the traditional SR model typically consists of 2 to 12 attendees [32]. Consequently, this feasibility study will aim to recruit between 4 and 10 participants and will not be designed or powered to evaluate the effectiveness of online SR; the absence of a comparator condition and the small sample size will preclude inferential conclusions about efficacy.

### Recruitment

International study recruitment is planned from November 2025 to March 2026. Potential participants will be identified through clinician referral at patient identification centers within the South Central Regional Research Delivery Network and via study posters displayed in oncology waiting rooms. If required to meet recruitment targets, the study will also be promoted internationally, via cancer charities and social media platforms (ie, LinkedIn, X [formerly known as Twitter], and Facebook). Interested parties will contact the lead author ([name]) directly and will be asked to complete a consent form and a screening and demographics questionnaire, as well as 3 weekly staggered baseline outcome measures (Multimedia Appendix 2). These data points will be collected via Qualtrics (Qualtrics International Inc), the same online platform where participants will indicate their availability for taking part in the online SR intervention.

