### Study Design

The study uses a mixed methods, nonrandomized, multiple-baseline, within-subject design consistent with SCED methodology. The multiple baselines will be operationalized via 3 repeated preintervention assessments (at −2 weeks, −1 week, and week 0) to establish outcome measure stability. Afterward, participants will commence the 6-week intervention simultaneously. Participant or researcher blinding is not possible. Data collection points are shown in Table 2.

**Table 2. T2:** Data collection points.

	Screening (–4 wk)	Baseline 1 (–2 wk)	Baseline 2 (–1 wk)	Baseline 3 (0 wk)	Midintervention time point (3 wk)	Postintervention time point (6 wk)
Demographics (ie, age, gender, ethnicity, educational level, employment status, and treatment status [ie, in treatment or in remission or cancer free])	✓	✓				
Psychological well-being (SWEMWBS^a^) [55]		✓	✓	✓	✓	✓
Psychological distress (K10^b^) [56]		✓	✓	✓	✓	✓
World Health Organization quality of life instrument social domain subscale [57]		✓	✓	✓	✓	✓
Two global items (health and QoL^c^) from the EORTC QLQ-30^d^ [58]		✓	✓	✓	✓	✓
Exit survey (for dropout participants; Multimedia Appendix 3)—to be administered at any exit point						

a

SWEMWBS: Short Warwick-Edinburgh Mental Wellbeing Scale.

b

K10: Kessler Psychological Distress Scale.

c QoL: World Health Organization Quality of Life social domain subscale.

d

EORTC QLQ-C30: European Organisation for Research and Treatment of Cancer Quality of Life Questionnaire Core 30.

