## Results

This feasibility study received funding in October 2022 as part of a PhD scholarship. Recruitment started in November 2025 and continued until March 2026. At the time of manuscript submission in January 2026, a total of 6 individuals had registered their interest, of whom 2 met the eligibility criteria. The data analysis plan was developed in January 2025 to facilitate university and National Health Service Health Research Authority ethical submissions and registered on the Open Science Framework in May 2025 [66]. The analysis has not yet been implemented, with the intervention commencing in May 2026. Dissemination of findings is planned for November 2026 and will follow SCRIBE (Single-Case Reporting Guideline in Behavioral Interventions) guidelines [67]. The study timeline is summarized in Figure 1.

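### Screening falls one to seven months before session 1, not at −4 weeks, and the concurrent-therapy exclusion is tied to recruitment with no described re-check

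*Protocol article*

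**What the plan says.** All of the following is in the protocol article.

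- **Recruitment:** "International study recruitment is planned from November 2025 to March 2026". In the same section, people who make contact "will be asked to complete a consent form and a screening and demographics questionnaire, as well as 3 weekly staggered baseline outcome measures".
- **Study Design, Table 2:** screening is at −4 weeks. The three baselines are at −2, −1 and 0 weeks, followed by weeks 3 and 6.
- **Study Design, text:** after the baselines, "Afterward, participants will commence the 6-week intervention simultaneously".
- **Results:** "The analysis has not yet been implemented, with the intervention commencing in May 2026". By the January 2026 submission, "a total of 6 individuals had registered their interest, of whom 2 met the eligibility criteria".
- **Participants:** "participants must not be receiving other psychological interventions at the time of recruitment". The reason given is that concurrent specialized therapy could confound the reading of individual-level effects.
- **Preliminary Quantitative Outcomes:** each participant's change is judged by the reliable change index, with a threshold of 1.96, and shown on modified Brinley plots.

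Table 2 repeats demographics, including treatment status, at Baseline 1. Current psychological therapy is not among the items it lists at any time point.

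**The concern.** Table 2 implies that eligibility is settled four weeks before the first session. The calendar elsewhere in the article does not allow that for people screened as they are recruited. There is one common start, so early recruits wait much longer than late ones.

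This matters because of the therapy exclusion. The protocol adopts it specifically to protect individual-level interpretation but ties it to recruitment. Someone who was not in therapy in November and began counseling in February would satisfy the rule as written and stay in the study. The article itself describes long waits for psychological care, so such a start during the wait is plausible. In a study with no comparator, judged person by person, any resulting improvement could be read as a response to shared reading, and nothing in the visible data collection would show otherwise.

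**Working it through.** **Inputs**

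- Recruitment window (Recruitment): taken as 1 November 2025 to 31 March 2026.
- Session 1 (Results): May 2026. The day is not stated, so 1 to 31 May is used as a range. This is an assumption.
- One start date for all participants (Study Design).
- Scheduled screening (Table 2): −4 weeks, that is 4 × 7 = 28 days.
- Two people eligible by January 2026 (Results): latest possible date taken as 31 January.
- Target sample (Participants): 4 to 10.

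**Step 1. Can the plan's own figure be reproduced?** Screening date = session 1 − 28 days.

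- Session 1 on 1 May gives 3 April 2026.
- Session 1 on 31 May gives 3 May 2026.

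Both dates fall after recruitment closes on 31 March, so the −4 week figure cannot be reproduced for anyone screened inside the window.

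**Step 2. What interval do the stated dates give?** Interval = session 1 − screening date.

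| Screened | Session 1 on 1 May | Session 1 on 31 May |
|---|---|---|
| 1 Nov 2025 | 181 days (25.9 weeks) | 211 days (30.1 weeks) |
| 31 Jan 2026 | 90 days (12.9 weeks) | 120 days (17.1 weeks) |
| 31 Mar 2026 | 31 days (4.4 weeks) | 61 days (8.7 weeks) |

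The range is 31 to 211 days, or 1.0 to 6.9 months. The excess over 28 days runs from 31 − 28 = 3 days to 211 − 28 = 183 days. For the two people eligible by January the interval is at least 90 days.

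**Step 3. Do the baselines share the problem?** No. The abstract and Study Design both set them at −2, −1 and 0 weeks before the common start. Weeks 3 and 6, the mid- and postintervention points, lie on the same axis, so week 0 is the intervention start. The first baseline would fall between 17 April (1 May − 14 days) and 17 May (31 May − 14 days). The baselines are therefore 0 to 2 weeks old at session 1.

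**Step 4. What weight does one affected participant carry?** With 10 participants, 1/10 = 10%. With 4 participants, 1/4 = 25%.

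**The case against.** **Stale baselines.** A reader might infer from Recruitment, which lists the baselines alongside consent and screening, that they are also completed on first contact. Three weekly forms begun on the day of recruitment would end 31 − 14 = 17 to 211 − 14 = 197 days before session 1. The documents do not support this reading. Recruitment gives no date for the baselines, and a loose list does not override the explicit schedule in Study Design and the abstract.

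**Distorted attrition.** A reader might also infer that losses during the wait will count as dropout from the intervention. Nothing in the article says so. Recruitment yield, reasons for declining or dropping out, and session attendance are listed separately, and the exit survey is given whenever withdrawal occurs. Separating the losses is useful reporting, not the correction of a stated error.

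**Treatment status.** Both active treatment and remission are admitted, so a change of status does not affect eligibility, and Table 2 already asks again at Baseline 1. There is no eligibility problem here.

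**Size of the mismatch.** At the near edge it is only 3 days. The start day is unknown, and Figure 1, the timeline, is not shown. Some screening might also have taken place after March. These points stand for late recruits. They do not help the two people already judged eligible by January.

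**Unseen forms.** Multimedia Appendix 2 may ask about therapy again. That stands as a limit: one can say only that the visible text describes no re-check.

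**Limited impact.** Individual outcomes are secondary and descriptive, and the article disclaims conclusions about efficacy. That limits the consequence. But the article sets the exclusion to protect this same individual-level reading, so a check that may be months old weakens its stated purpose.

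**Timing.** The section on intervention development carries an August 2026 exchange-rate date. Week 6 from a May start falls between 12 June and 12 July (start + 42 days), so the group may already have run. This affects how the fix is made, not whether the point holds.

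**Conclusion.** The point holds for screening and eligibility. The −4 week label conflicts with the stated calendar: screening within the recruitment window precedes session 1 by 31 to 211 days, and by at least 90 days for the two people eligible by January. The therapy exclusion is tied to recruitment, so the rule as written would keep a participant who began therapy during a wait of one to seven months. Each such participant is 10% to 25% of the target sample.

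This rests on the recruitment months being read as whole months, on an unstated start day anywhere in May, and on there being no re-check in the forms that are not shown. How many people will start therapy is unknown, and the article gives no figure from which to estimate it.

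The conclusion does not extend to the timing of the baselines, and it does not show that the attrition figures are wrong. It is a specific source of bias in the individual-level results that is cheap to reduce, and it should be addressed.

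**What to change.** 1. Reconcile Table 2 with the calendar by describing screening as done at enrolment, with a variable interval to session 1.
2. Re-ask current psychological therapy, with start date, at Baseline 1 and at weeks 0, 3 and 6 on the existing Qualtrics forms.
3. Flag any participant who started therapy on the individual plots and in the interpretation of that person's reliable change.
4. Report each participant's screening-to-session-1 interval.
5. Report losses before session 1 and losses after it separately.

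The cost is one short extra item per form and a minor amendment. If the group has already run, items cannot be added prospectively. Therapy start dates can then be asked retrospectively, accepting some recall error. The corrected label, the interval and the separated losses can still be reported with the findings planned for November 2026.
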